## Abstract

Quantitative running gait analysis is an important tool that provides beneficial outcomes to injury risk/recovery or performance assessment. Wearable devices have allowed running gait to be evaluated in any environment (i.e., laboratory or real-world settings), yet there are a plethora of different grades of devices (i.e., research-grade, commercial, or novel multi-modal) available with little information to make informed decisions on selection. This paper outlines a protocol that will examine different grades of wearables for running gait analysis in healthy individuals. Specifically, this pilot study will: 1) examine analytical validity and reliability of wearables (research-grade, commercial, high-end multimodal) within a controlled laboratory setting; 2) examine analytical validation of different grades of wearables in a real-world setting, and 3) explore clinical validation and usability of wearables for running gait analysis (e.g., injury history (previously injured, never injured), performance level (novice, elite) and relationship to meaningful outcomes). The different grades of wearable include: (1) A research-grade device, the Ax6 consists of a configurable tri-axial accelerometer and tri-axial gyroscope with variable sampling capabilities; (2) attainable (low-grade) commercial with proprietary software, the DorsaVi ViMove2 consisting of two, non-configurable IMUs modules, with a fixed sampling rate and (3) novel multimodal high-end system, the DANU Sports System that is a pair of textile socks, that contain silicone based capacitive pressure sensors, and configurable IMU modules with variable sampling rates.

**Clinical trial registration: Trial registration**: NCT05277181.

## Introduction

Running is one of the most popular sport and recreational activities worldwide, as well as being a core component to many sports [1]. With the growing popularity of running, a concurrent increase in the incidence of running related injuries has also been reported [2, 3]. It is well established that an abnormal running gait is a contributing factor to running related injuries [4]. Quantitative running gait analysis, as a (clinical) tool for minimising injury risk and as a performance measure, has been well documented in the literature [5–7], with improvements in running gait, leading to maximized mechanical efficiency thus enhancing performance, and reducing injury risk [8].

A variety of methods exist to examine running gait, in low-resource settings practitioners have largely been limited to the use of subjective clinical observations using rating scales (e.g., The High-Level Mobility and Assessment tool), and/or 2D video analysis, which may not be sensitive to subtle changes in performance with training or injury [9–11]. To analyse less readily identifiable outcomes, such as fine motor movement in spatiotemporal characteristics (e.g., stride length, stride time, cadence, speed), kinematic (e.g., angular velocity and joint angles) and kinetic (e.g., ground reaction forces, GRF), more cumbersome and expensive traditional (reference/gold-standard) gait laboratory equipment are required (e.g., 3D motion capture, force plate equipment, instrumented treadmills). Equally, use of laboratories for running gait assessment is further limited due to the need for trained practitioners to collect and analyse data and requirement to attend a bespoke setting. Furthermore, traditional lab-based approaches provide limited understanding of running from ‘real-world’ environments [12–14] and often use constrained protocols that may not represent usual running behaviour, such as unnatural force platform targeting [15]. Numerous studies have sought to overcome this issue by using instrumented treadmills, however, further studies demonstrate inconsistencies in running gait between over-ground and treadmill running [16]. In order to enhance understanding of running gait, further research in a natural running environment is required [15].

Wearable devices offer an alternative to overcome traditional assessment limitations and are becoming increasingly popular amongst runners, coaches and clinicians [17]. Wearables using accelerometers, gyroscopes, and magnetometers, applied individually or in combination as an inertial measurement unit (IMU), and ‘pressure-sensitive’ insoles enable examination of a combination of spatiotemporal, kinetic, and kinematic variables and have become a viable alternative due to their portability and affordability [18]. Wearables can quantify running gait outcomes in any setting (i.e., laboratory, outdoor/real-world), and have the potential to be an effective tool to capture the full duration and nuances of a run, which ultimately may enhance understanding of running performance, fatigue, and injury mechanisms [19, 20].

Wearables have seen an expansive increase in personal use, as well as application in industry and research. However, there is a lack of evidence for validity, reliability, and application of wearables for running gait assessment [19–22], with different grades of devices receiving different levels of testing. For example, many commercial devices receive little / no validation testing before commercial launch, whereas research-grade devices that are developed by academic researchers tend to receive validation testing but may not be applied within relevant populations to inform clinical or performance outcomes [18–22]. Therefore, this pilot study aims to examine the validity, reliability, and application of various grades of wearable devices (research-grade, commercially available and novel multi-modal) for running gait assessment. The presented protocol will follow an evidence-based approach to drive the appropriate adoption of fit-for-purpose wearable technologies [23]. An evaluation of the usefulness and utility is only applicable after gaining evidence and assurance that the underlying data obtain valid and reliable results to answer a given question [23].

### Analytical validation aims

***Laboratory validation***: Determine the concurrent validity and test re-test reliability of wearables (research-grade, commercial and novel multimodal devices) for running gait analysis against gold-standard reference measures in adult runners.***Real-world validation***: Investigate concurrent validity of real-world running gait as measured by different wearables (research-grade, commercial and novel multimodal devices) in adult runners.

### Exploratory clinical validation aims

Explore differences in running gait outcomes within different clinical (injured vs non-injured) and performance (elite vs novice) groups.Explore relationships between real-world running gait and demographic characteristics (e.g., sex, age) in different clinical and performance groups (e.g., those with a previous injury or different performance level).Investigate the usability of the wearable devices in adult runners.

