### Participants

A total of 80 runners with a variety of training experience will be recruited and assessed within laboratory (n = 40) and real-world environments (n = 40). The common inclusion and exclusion criteria are outlined in Table 1.

**Table 1 pone.0291289.t001:** Participant criteria.

Inclusion Criteria	Exclusion Criteria
Aged 18–70 years.	Medical history of disability that affects running gait safety or ability to follow instructions/tasks.
English as a first language or fluency.	
Able to run 5km without stopping.	Known illness or disease that would prevent their participation in strenuous physical activities (e.g., cardio-respiratory conditions or acute COVID-19).
Take part in running of some form at least twice per week (e.g., 5km run).	
	If the participant is unable to comply with the testing protocol, they will not be recruited.

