#### Real-World environment testing

Data from the novel multimodal, commercial, and research-grade wearables will be collected within real-world environments to test the clinical / performance validity of the wearables (i.e., can they differentiate or provide meaningful data on relevant populations). Recruitment for the real-world environment testing began in June 2023 with an expected end date October 2023.

*Participants*. Within the real-world environment testing 40 individuals, specifically novice/amateur (n = 20) and expert/sub-elite (n = 20) running performance level. Performance level will be based on their 5km running time (i.e., age graded performance % [35]).

*Wearable location*. Each participant will be equipped with the DANU Sports System (socks on both feet), two Axivity AX6 sensors attached to the shoelaces and two DorsaVi ViMove2 sensors on the tibia.

*Running procedures*. All participants, regardless of performance level, will be asked to complete a 5km run on a standardised route in North-East England. The course will be run on a mixture of trail paths and concrete paths, with 174ft elevation gain throughout. Information about conditions (e.g., environment and shoes) and objective load data (e.g., time and pace) will be collected. Participants will wear their own running shoes.

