To examine the analytical (concurrent) validation of running gait outcomes measured in real-world settings from the various grades of wearables in all real-world testing participants (n = 40), we will compare outcomes across the wearable devices (research, commercial and novel multi-modal) through widely used measures of agreement. The absolute difference, r, ICC, the level of agreement through the Bland Altman plots, 95% LoA, RMSEs will be calculated to evaluate agreement between outcomes generated by each wearable [48].

*Exploratory clinical validation analysis*. To provide an initial exploration of clinical (performance) validation, we will investigate group difference and relationships with clinically (or performance) relevant measures. For group differences (e.g., previous injury history or performance level), analysis of co-variance (ANCOVA), will be conducted to assess for differences between groups (injured vs non-injured, or elite vs novice) in the individual running gait outcomes (e.g., ground contact time etc.) from the novel multimodal, commercial and research-grade wearable devices during the running tasks, while controlling for demographics that are significantly related to the running gait outcomes. Relationships between running gait outcomes and demographic variables (e.g., sex, age, height, weight etc.) within groups (injured vs non-injured, or elite vs novice) will be completed through Pearson correlations within each grade of wearable device (research, commercial, multimodal).

To examine the usability of the wearable devices the SUS scores for each wearable will be calculated and visualised. To investigate differences in participant perception of the usability for each grade of wearable, separate analysis of variance (ANOVA) tests will be performed. The ANOVAs will determine the differences between the SUS scores within the different device grades between participant groups (e.g., injury history, performance level). The relationships between the SUS scores, demographics (e.g., sex, age, age-grade performance), and wearables characteristics (e.g., price, weight, and battery life) will be explored using Pearson correlations [39]. The strength of the correlation will be assessed based on Cohen’s criteria: correlations < 0.30 are considered small, correlations between 0.30 and 0.50 will be considered medium, and correlations > 0.50 are considered strong [53].

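### Within performance groups formed on age-graded 5 km time, the planned correlations of real-world gait with age and sex cannot be separated from pace; a pace-adjusted correlation should be reported beside them

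*Protocol article*

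**What the plan says.** All references are to the protocol article.

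- **Aim** (Exploratory clinical validation aims): "Explore relationships between real-world running gait and demographic characteristics (e.g., sex, age) in different clinical and performance groups".
- **How the performance groups are formed** (Real-World environment testing, Participants): "specifically novice/amateur (n = 20) and expert/sub-elite (n = 20) running performance level", with the rule "Performance level will be based on their 5km running time (i.e., age graded performance % [35". No cut-off percentage is given.
- **The run** (same section, Running procedures): participants "will be asked to complete a 5km run on a standardised route in North-East England". No speed or effort is prescribed. The fixed speeds of 8, 10, 12 and 14 km/h belong to the laboratory treadmill only.
- **Pace data** (same place): "objective load data (e.g., time and pace) will be collected". No planned gait analysis uses them.
- **The analysis** (Statistical analysis, Exploratory clinical validation analysis): each gait outcome is to be related to sex, age, height and weight inside each group. The method stated for this is that it "will be completed through Pearson correlations within each grade of wearable device (research, commercial, multimodal". No pace term is named.
- **Eligible ages** (Table 1): "Aged 18–70 years".

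**The concern.** An age-graded percentage rates a runner against a standard for that age. Two runners with the same percentage but different standards run at different absolute speeds. A group that is narrow in age grade is therefore not narrow in pace, and what remains of the pace variation follows age more closely than it does among runners at large. If the standard also differs by sex, the same holds for sex.

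To the extent that a gait outcome depends on pace, a raw correlation of that outcome with age then mixes two things: gait changing with age at a given pace, and older runners in the group running slower. The planned coefficient cannot tell them apart, although the variable that could separate them is recorded.

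What is at stake is how the second exploratory aim is read. All three devices record the same run, so for an outcome that depends on pace the association would tend to appear on each device that measures it. Agreement across devices would then look like replication without being independent confirmation.

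**Working it through.** **The plan's own figure.** The sample size section gives 20 per group by rule of thumb, with no effect size, SD or power, so there is nothing to reproduce. What follows from n = 20 (two-sided 5% assumed) is the critical correlation: t(18 df) = 2.101, so |r| = 2.101/√(18 + 2.101²) = 0.444.

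**Model used for the check.** Speed = age-grade % × standard speed for age and sex × effort noise. Gait depends on speed only, with no direct age or sex effect. None of the following inputs comes from the protocol:

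- age grade uniform 40–60% (novice) or 70–85% (expert);
- standard speed flat to age 35, then falling linearly to lose 20–30% by age 70;
- female/male standard ratio 0.88;
- effort noise SD 0–0.10 on log speed;
- pace-gait correlation 0.5–0.8.

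**Step 1: within-group correlation with pace.** For age it is −0.39 to −0.77 if ages span 18–70, but only −0.15 to −0.41 if they span 20–50. For sex it is −0.31 to −0.71, conditional on sex-specific grading.

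**Step 2: what that induces in gait.** Induced r(age, gait) ≈ r(age, pace) × r(pace, gait). The strongest setting gives −0.77 × 0.8 = −0.62. The weakest gives −0.15 × 0.5, about −0.07. (For an outcome that falls as pace rises, the sign reverses.) So the induced correlation runs from negligible to above the protocol's own 0.50 threshold for a strong correlation.

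**Step 3: does the grouping rule matter?** Splitting one simulated population in different ways gives:

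| Grouping | r(age, pace) | r(sex, pace) |
|---|---|---|
| None (all runners) | −0.11 to −0.44 | −0.26 to −0.28 |
| Age-graded % | −0.17 to −0.70 | −0.35 to −0.56 |
| Raw 5 km time | −0.08 to −0.37 | −0.16 to −0.34 |

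The link exists without grouping, and age-grade grouping strengthens the correlation. It does not change the underlying slope. With ages 18–70, 0.8% of speed lost per year after 35 and age grade uniform 40–85%, log pace falls by 0.0068 per year of age in all runners, in the novice group and in the expert group alike. Since r = slope × SD(age)/SD(log pace), r rises only because the other variation in pace shrinks: from about −0.41 ungrouped to −0.59 and −0.74 within groups. For ages 20–50 it goes from −0.16 to −0.26 and −0.38.

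**Step 4: how often a significant result appears, single tests.** With gait depending on pace alone and n = 20, the unadjusted Pearson test is significant in 7–88% of groups for age and 11–66% for sex. With pace partialled out, each test is significant in about 5–6%.

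**Step 5: like for like, at least one of age or sex.** This uses a second parameter set: within-group age-grade SD 3–6 points, women's standard 11% slower, half women, 3% day-to-day noise, pace-gait correlation 0.6–0.8. Unadjusted, at least one of the two is significant in about 28–93% of groups. If the yearly loss after 35 is set as steep as 1.0%, the top reaches 96%. With pace partialled out, the same two-test rate is about 8–10%, in line with 1 − 0.95² = 0.0975 for two independent tests at 5%.

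**The case against.** The strongest reply is that nothing here is an artefact. If older runners are slower and slower runners move differently, then age is related to gait, and an unadjusted correlation describes that truthfully. Pace lies on the path from age to gait, so partialling it out answers a different question. The aim speaks of relationships, not of relationships at a given pace. It is exploratory, and the protocol says that later research can control for relevant variables.

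Much of this stands. A reader might infer that age grading manufactures the correlation by construction, or that the planned coefficients will largely report pace. The documents support neither reading. The slope of pace on age is the same with and without the grouping, and only the correlation rises. With ages 20–50 the induced age correlation can fall below 0.1. The protocol gives no recruited age distribution, cut-offs, effort or pace-gait correlation from which the share due to pace could be fixed.

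Three further limits also stand:

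- The protocol says only that performance is age graded. That the standard is also sex-specific is an assumption, so the sex part is conditional.
- A reader might extend the point to the whole aim. The injury groups are formed on injury history, so the mechanism does not reach them.
- Table 2 includes outcomes such as symmetry and foot-strike pattern, for which no dependence on pace is stated. It cannot be said that most outcomes would be affected.

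What the reply does not remove is the ambiguity. The plan does not label the correlation as including pace, and a reader of the results could take it for an effect of age on running style. The grouping rule makes that misreading more likely, because it raises r within the groups where it will be reported.

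**Conclusion.** The point holds in a limited form. In the performance groups of the real-world arm, the planned within-group correlations of gait with age, and with sex if grading is sex-specific, cannot be distinguished from a relationship through pace, and may reflect pace in substantial part. Age-grade grouping raises the correlation but does not create it.

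The figure of about 28–93% against 8–10% for at least one significant result is conditional on the assumed ages, age-grade spread, speed decline and pace-gait correlation, and on there being no direct age or sex effect. It shows what could happen, not what will. The unadjusted correlation remains a legitimate description once labelled. For an exploratory aim this is a cheap improvement rather than an error that invalidates the analysis.

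**What to change.** For the real-world performance groups:

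1. Keep the planned Pearson correlation of each gait outcome with each demographic variable, and state that it includes differences in pace.
2. Beside it, report the partial correlation (or a regression) given each runner's recorded mean pace over the 5 km route.
3. Draw conclusions about age or sex at a given pace only from the adjusted figure.

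The grouping rule and the injury-group analyses need no change for this reason.

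The cost is a change of analysis wording and one extra column in the results. No new data are needed, since time and pace are already collected. Each correlation loses one degree of freedom: the critical |r| at n = 20 moves from 0.444 (18 df) to 2.110/√(17 + 2.110²) = 0.456 (17 df), so intervals are slightly wider.

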## Materials and methods

### Study design

This is a cross-sectional study that will assess the validity and reliability of three grades of wearables (research, entry-level commercial and advanced / novel multimodal). The protocol was developed according to the Standard Protocol Items: Recommendations for Interventional Trials’ (SPIRIT) checklist [24], as appropriate (see S1 File). As this is a study protocol, no data has been included and conforms to PLOS data policy. The overall schedule and time commitment for trial participants are depicted in Fig 1 and S1 File.

**Fig 1 pone.0291289.g001:**
[figure not shown]
SPIRIT diagram. The overall schedule and time commitment for study participants for both a) laboratory testing and b) real-world environment testing.

### Ethical approval and trial registration

A Northumbria University research ethics committee granted ethical approval (Ref: 21603 and 33358) and this study conforms to the Declaration of Helsinki. The trial has been reviewed and registered with Clinicaltrials.gov (NCT05277181).

### Participants

A total of 80 runners with a variety of training experience will be recruited and assessed within laboratory (n = 40) and real-world environments (n = 40). The common inclusion and exclusion criteria are outlined in Table 1.

**Table 1 pone.0291289.t001:** Participant criteria.

Inclusion Criteria	Exclusion Criteria
Aged 18–70 years.	Medical history of disability that affects running gait safety or ability to follow instructions/tasks.
English as a first language or fluency.	
Able to run 5km without stopping.	Known illness or disease that would prevent their participation in strenuous physical activities (e.g., cardio-respiratory conditions or acute COVID-19).
Take part in running of some form at least twice per week (e.g., 5km run).	
	If the participant is unable to comply with the testing protocol, they will not be recruited.

#### Recruitment

An advertisement poster and email text invitation will be sent via email to Northumbria University running clubs and running clubs within England. Recipients will be asked to pass on the recruitment poster to potential interested parties (i.e., family or friends). Recruitment began in January 2022. Those interested will then be given a participant information sheet and a letter concerning the study and consent. Written, informed consent will be collected from all participants.

### Equipment

#### Reference standard: 3D motion analysis

A 14-camera motion analysis system (VICON, Oxford, UK), sampling at 250Hz will be used. Calibration of the Vicon system will be conducted before each data collection. Sixteen reflective markers will be placed on the participants lower limb before testing, and a static calibration trial will be initially collected to form a musculoskeletal model [25]. Using a small amount of double-sided tape, the place of markers will be attached bilaterally to the following landmarks: anterior superior iliac spine, posterior superior iliac spine, mid-lateral thigh, lateral knee joint line, lateral mid-shank, lateral malleoli, calcaneal tuberosity, and base of the second metatarsal.

The participants’ specific information of weight, height, ankle width, knee width, and leg length (from posterior iliac spine to medial malleolus) will be measured in the lower body model [26]. The Plug-in-Gait (PiG) lower body model will be used to analyse movement at the joints and evaluate all parameters. The lower body will be modelled as seven segments (one pelvis, two thighs, two shanks, and two feet). A normal gait cycle will be defined from the initial heel-to-heel contact with the same limb. Additional information of the PiG calculations can be found on Vicon’s website. Fig 2 shows the participants’ setup of the anterior, lateral, and posterior views with the markers in place.

